### Secondary endpoints

Clinical signs and symptoms in uncomplicated LUTIs in women.Frequency and timing of relapse of symptoms and/or bacteriuria.Bacteriological findings (i.e. ESBL producing bacteria).Complications (i.e. urosepsis and/or pyelonephritis) within 28 days.

### Definitions

Clinically cured is defined as cumulative symptom score of <2.Clinical relapse is defined as initial clinically cured followed by cumulative clinical score of ≥2 at day 28.Bacteriologically cured is defined as significant reduction (i.e. ≥ 10^2^ fold decrease in uropathogenic bacteria) or potentially full eradication of uropathogenic bacteria (i.e. sterile culture or asymptomatic contaminations of non-uropathogenic bacteria).Bacteriological relapse is defined as initially bacteriologically cured followed by significant growth at day-28, with the same bacteria. Growth of other uropathogenic bacteria is defined as reinfection.

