#### Questionnaires

The GP will receive an inclusion-questionnaire that he/she will fill out on day 0 (inclusion day). The questionnaires his will include age, positive inclusion criteria (i.e. LUTI symptom load), exclusion criteria, debut date of symptoms, and annual incidence of LUTI. All participants will be given a diary-questionnaire for day 0 to day 7*.* In which they daily will answer questions on LUTI symptoms, score them of severity on daily bases and report on which day they feel completely cured (i.e. back to habitual conditions). They will also be asked to register impairment in daily life activities and quality (i.e. work, physical activity, sleep, mental well-being) similar to the symptom score, previous UTI, travel, weight (i.e. >70 kg) possible adverse effects, adherence to the therapy, use of analgesics and other optional information. The patient will also receive a second follow-up questionnaire which need to be filled out once anytime around day-28 (i.e. possible symptoms or side effects since end of therapy, current status of questions asked in the symptom-diary). All questionnaires on symptoms are constructed according to the validated questionnaires for LUTI symptom score [16]. They will be submitted together with the urine samples. All of the patients’ questionnaires will be so patients can easily understand and answer the questions.

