### Second medical consultation

Patients will be told at recruitment to visit the GP again if she develops worsening of symptoms or not experiencing any symptom relief during the study period. In that case the GP is able to choose a new treatment strategy for the patient and will have the potential microbiological diagnostic answers (i.e. from pre-treatment urine sample) to take in consideration in this approach.

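### Clinical relapse is read only from the day-28 score, which does not fit a secondary endpoint of frequency and timing of relapse

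*Protocol article*

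**What the plan says.** Four parts of the protocol article bear on this point.

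- **Outcome, Definitions.** Cure is a threshold on the symptom sum: "Clinically cured is defined as cumulative symptom score of <2". Relapse is read on one day: "Clinical relapse is defined as initial clinically cured followed by cumulative clinical score of ≥2 at day 28".
- **Secondary endpoints.** The quantity to be reported is "Frequency and timing of relapse of symptoms and/or bacteriuria". Procedures to evaluate endpoints adds that the day-28 questionnaire is to reveal relapse or reinfection of any kind, as well as hospital admission and repeat consultation.
- **Questionnaires.** "All participants will be given a diary-questionnaire for day 0 to day 7", with symptoms scored daily. After that there is one "second follow-up questionnaire which need to be filled out once anytime around day-28", covering "possible symptoms or side effects since end of therapy, current status of questions asked in the symptom-diary". Follow-up adds a call or text message at about days 9–11, but describes no symptom score at that contact.
- **Second medical consultation and Criteria for termination from the study.** Women are told to "visit the GP again if she develops worsening of symptoms" or if they get no relief, and the GP may then change the treatment. A woman with treatment failure leaves the study.

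**The concern.** The definition and the endpoint it serves do not match. A rule that looks at one day can count only relapses still present on that day, and it gives all of them the same time. It therefore measures how many cured women are symptomatic at day 28, which is not the frequency of relapse and says nothing about its timing. It is also narrower than the use of the day-28 questionnaire described in Procedures to evaluate endpoints.

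This matters because of what the trial compares. According to Intervention, the arms differ only on days 4 and 5, and the proportion cured in the first co-primary endpoint is read at day four. Symptoms that return after the shorter course are a plausible place for a difference to show, and the relapse endpoint is where they would be reported. The article also says, under Scientific and societal perspective, that a finding of non-inferiority would support keeping the 3-day regimen. An undercounted relapse endpoint would be weak evidence for or against that.

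**Working it through.** **1. What the rule does to particular courses.** Each woman below was first clinically cured (score below 2).

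| Course after cure | Is the recurrence in the data? | Result under the day-28 rule |
|---|---|---|
| Score ≥2 on day 6, below 2 at day 28 | Yes, dated by the diary | Not a relapse |
| Symptoms on day 12, settled or retreated, below 2 at day 28 | Only by recall or second consultation | Not a relapse |
| Symptoms on day 12, handled as treatment failure and terminated | Possibly through the GP | Day-28 score may be missing; not stated how she is counted |
| Symptoms from day 12, still ≥2 at day 28 | Yes | Relapse, at day 28 |
| First symptoms again at day 28 | Yes | Relapse, at day 28 |

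The last two rows have different onsets and the same recorded time. In the third row, the per-protocol set, and the need-to-treat set drawn from it, exclude dropouts.

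**2. The plan's own figures.** The article states no figure for relapse. Its stated sizes come from Power analyze: 90% v 75%, two-sided 0.05, power 0.80.

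- Uncorrected two-proportion formula: n = [1.960·√(2 × 0.825 × 0.175) + 0.842·√(0.09 + 0.1875)]² / 0.15² = 99.5, so 100 per group.
- With continuity correction: (99.5/4)·[1 + √(1 + 4/(99.5 × 0.15))]² = 112.5, so 113 per group, as stated.
- Fall-out of 30%: 113/0.7 = 161.4 and 161/0.7 = 230.0, matching the stated 161 and 230.

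None of these uses the relapse definition.

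**3. Size of the loss (illustration on assumed rates).** Let a share f of true relapses score below 2 at day 28, equally in both arms, and be recorded as no relapse. Then recorded rate = true rate × (1 − f), and recorded difference = true difference × (1 − f). The true rates below are assumptions.

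Assumed true relapse 20% v 10%. Power is two-sided at 0.05 with 161 or 113 women per group, by the normal approximation without continuity correction:

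| f | Recorded rates | Difference (points) | Power, 161 | Power, 113 |
|---|---|---|---|---|
| 0 | 20% v 10% | 10 | 71% | 56% |
| 0.25 | 15% v 7.5% | 7.5 | 57% | 43% |
| 0.50 | 10% v 5% | 5 | 40% | 30% |
| 0.75 | 5% v 2.5% | 2.5 | 22% | 17% |

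With lower assumed rates of 10% v 5%, f = 0.5 gives 5% v 2.5%. With f = 0.8 it is 0.10 × 0.2 = 2% v 0.05 × 0.2 = 1%, so a 5-point difference becomes 1 point. The ratio stays 2:1 throughout. Fisher's exact test, which the article names, is more conservative than this approximation, and only cured women can relapse, so actual power would be somewhat lower in every row.

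**The case against.** The strongest reply is that the trial's data are better than its definition. The diary observes and dates any return of symptoms up to day 7, the day-28 form asks about symptoms since the end of therapy, and second consultations are to be captured. The form is not shown and may already ask for dates. This stands, and it rules out the reading that timing of relapse cannot be measured at all. The gap in scheduled scores covers only days 8–27. It does not rescue the definition, which uses none of this information.

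Three other inferences are tempting and are not supported:

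- **That every retreated woman is recorded as relapse-free.** Intervention describes treatment failure as continuing or worsening symptoms, and treatment failures are terminated. She may be missing instead, and the article does not say which. Either way, no relapse is counted.
- **That most relapses will be treated before day 28.** No document gives a rate.
- **That the rule biases every comparison toward no difference.** With an equal undercount in both arms the ratio is preserved. The absolute difference and the power fall.

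It is also fair to say that relapse is only a secondary endpoint. A woman who relapses on day 6 still counts as cured at day four, but that is the co-primary endpoint working as written and does not come from the relapse rule.

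**Conclusion.** The point holds in a limited form. The day-28 definition conflicts with the stated secondary endpoint and with the stated use of the day-28 questionnaire. If followed, it gives an undercounted and undated relapse endpoint. This is not detail left to an analysis plan, because the article fixes the rule.

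The size cannot be stated from the documents. The absolute difference falls by the share of relapses that score below 2 at day 28, on the assumption that this share is equal in both arms; if it differs, the ratio would change too. Women missing after termination would add a loss that the article does not let one estimate. The co-primary endpoints and the sizes of 113, 161 and 230 per group are untouched.

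**What to change.** Reconcile Definitions, Secondary endpoints and Procedures to evaluate endpoints by defining clinical relapse as the first of the following in a woman who is already clinically cured, counted from one fixed day common to both arms (for example day 4, when the arms first differ) up to day 28:

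- a diary score of 2 or more;
- return of LUTI symptoms reported on the day-28 questionnaire;
- a second consultation or new antibiotic for returned LUTI symptoms;
- a score of 2 or more at day 28.

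Date each relapse at the first such event. Count women terminated because symptoms returned after cure as relapses. Do not count antibiotic changes made only because of a laboratory finding, as described under In trial intervention. Report the day-28 score separately.

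The fixed start day is needed because the cure threshold is low: without it, a change from 1 to 2 points while both arms are on active drug would count as a relapse.

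The cost is a change of wording, since diary scores, symptoms since therapy and second consultations are already to be collected. The day-28 form may need an onset-date field if it has none. The downside is that events between days 8 and 27 rest on recall or on the second consultation, so their dates will be less exact than those from the diary.

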#### Microbiological diagnostics

One pre-treatment urine sample (day 0) with optional urine-dipstick, and two control urine samples (day 8–10 and day 28–30, respectively) will be sampled from the patient. The three urine samples will be sent to the DCM, Hvidovre University Hospital, Denmark, for examination of the presence and count of uropathogenic bacteria. In presence of significant bacteriuria (i.e. ≥10^3^ bacteria/ml [*E. coli*] / ≥10^4^ bacteria/ml [other uropathogenic bacteria]) the isolates will also be examined for resistance mechanisms and patterns, minimal inhibitory concentration (MIC) to mecillinam (i.e. by E test, AB Biodisk, bioMe’rieux, Marcy-l’E’ toile, France) and determining the bacterial specimen (i.e. MALDI-TOF, Brukner, Germany). All urine samples will processed according to laboratory routine and susceptibility tested according to EUCAST guidelines [18]. During the study all significant uropathogenic isolates will be stored at minus 80 °C. At the end of the study these isolates will be genetically examined to determine their more specific identity/type, i.e. so we can evaluate if the potential relapse is either a true relapse or a reinfection (i.e. the same or different type of bacterial specimen).

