## Outcome

### Primary endpoint

We have two co-primary endpoints:
**Co-primary endpoint no. 1** –clinical efficacy (i.e. which group will be clinically cured fastest and proportion of patients cured at day four).
**Co-primary endpoint no. 2** – bacteriological efficacy (i.e. proportion of patients bacteriologically cured at first control urine sample).

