## Power, sample size and analysis

### Definitions

The intention-to-treat (ITT) analysis will be consisting of all included patients (i.e. patients that present with symptoms of uncomplicated LUTI and are included in the study). The per-protocol (PP) analysis will be consisting of all the patients that follow-up with clinical and bacteriological data (i.e. excluding the dropouts). The need-to-treat (NTT) analysis will be stratified from the PP analysis to only include patient with true uncomplicated LUTI (i.e. symptoms and significant bacteriuria, only isolates susceptible to mecillinam).

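### Bacteriological cure by a 100-fold fall has no ceiling on the remaining count, so it conflicts with the protocol's own limit for significant bacteriuria in co-primary endpoint 2

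*Protocol article*

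**What the plan says.** All references are to the protocol article.

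- **Endpoint** (Outcome, Primary endpoint). Co-primary endpoint 2 is "bacteriological efficacy (i.e. proportion of patients bacteriologically cured at first control urine sample".
- **Cure** (Outcome, Definitions). The first route reads "Bacteriologically cured is defined as significant reduction (i.e. ≥ 10^2^ fold decrease in uropathogenic bacteria". The second follows directly: "or potentially full eradication of uropathogenic bacteria (i.e. sterile culture or asymptomatic contaminations of non-uropathogenic bacteria". The two are joined as alternatives: "fold decrease in uropathogenic bacteria) or potentially full eradication of uropathogenic bacteria (i.e. sterile culture".
- **Limit** (Microbiological diagnostics). Isolates are worked up further "In presence of significant bacteriuria (i.e. ≥10^3^ bacteria/ml [*E. coli*] / ≥10^4^ bacteria/ml [other uropathogenic bacteria".
- **Relapse** (Outcome, Definitions). "Bacteriological relapse is defined as initially bacteriologically cured followed by significant growth at day-28, with the same bacteria". Frequency and timing of relapse is a secondary endpoint.
- **Use of the limit** (Power, sample size and analysis, Definitions). The need-to-treat (NTT) set keeps only patients with "true uncomplicated LUTI (i.e. symptoms and significant bacteriuria, only isolates susceptible to mecillinam".

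The Outcomes paragraph of the Discussion gives the purpose of the control urines: to establish that the organism has gone and will not bring symptoms back later.

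**The concern.** One section measures bacteria against a fixed count and another measures cure against the patient's own starting count. Nothing ties the two together. Because the two routes to cure are alternatives, a large relative fall is enough, however many bacteria are left. A patient with a high starting count can therefore be a success in a co-primary endpoint with a control urine that the same protocol would call significantly bacteriuric.

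The relapse definition compounds this. It takes cure from the relative rule and renewed growth from the significance rule, so a count that never dropped below the limit can satisfy both. The planned typing of isolates does not help: it separates the same strain from a different one, and so relapse from reinfection, but not relapse from persistence.

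At stake are the meaning of the cure proportion in co-primary endpoint 2 and the cleanness of the relapse endpoint.

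**Working it through.** **Inputs.** The 100-fold rule and the eradication rule come from Outcome, Definitions. The limits L = 10^3/ml (E. coli) and L = 10^4/ml (other uropathogens) come from Microbiological diagnostics. No outside figure is needed.

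**Cut-offs.** For a baseline count B, the relative rule scores cure when the control count is at most B/100. Bacteriuria is significant when the control count is at least L. Both hold together when the control count lies between L and B/100, which requires B ≥ 100 × L:

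- E. coli: 100 × 10^3 = 10^5/ml
- other uropathogens: 100 × 10^4 = 10^6/ml

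| Baseline (per ml) | Highest count still scored cured, B/100 | At or above E. coli limit? | At or above limit for others? |
|---|---|---|---|
| 10^3 | 10^1 | no | no |
| 10^4 | 10^2 | no | no |
| 10^5 | 10^3 | yes (boundary value only) | no |
| 10^6 | 10^4 | yes | yes (boundary value only) |
| 10^7 | 10^5 | yes | yes |
| 10^8 | 10^6 | yes | yes |

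**Cured but significantly bacteriuric.** E. coli from 10^7 to 10^5/ml is a 10^7/10^5 = 100-fold fall, hence a cure. The remaining count is 10^5/10^3 = 100 times the limit.

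**Cure followed by relapse without clearance.** The same patient with 10^5/ml at day 28 shows significant growth of the same bacteria after a recorded cure, hence a relapse. This needs a baseline of at least 10^7/ml. From 10^6/ml, a control count of 10^5/ml is only a 10-fold fall and is not a cure.

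**Below the limit but not cured.** E. coli from 10^4 to 5×10^2/ml is a 10^4/(5×10^2) = 20-fold fall. It fails the relative rule. It is neither sterile nor a contamination with non-uropathogens, so it fails the eradication rule too. Yet 5×10^2 is below 10^3.

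**Dependence on the laboratory's reporting range.** The article does not state it, so these are assumptions:

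- Counts reported no higher than 10^5/ml: the first conflict shrinks to the single value 10^3/ml for E. coli and disappears for other species.
- Counts reported no higher than 10^6/ml: it spans one log (10^3 to 10^4/ml) for E. coli and the single value 10^4/ml for others.
- No cap: it is as tabulated.

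**Sample size.** The stated 113 per group reproduces from 90% v 75%, two-sided 0.05, power 0.80, with continuity correction. The point does not rest on it.

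**The case against.** The strongest reply is that the rule is fixed in advance, applied identically in both arms and assessed blinded, and that the Discussion (Design and definitions) says the protocol follows earlier trials so that results can be compared. All of that stands. It means the rule does not by itself favour one arm. It does not remove the conflict between the two sections. Whether the earlier trials used a fold rule cannot be checked from the article.

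It is also fair that a conflict that can arise need not arise often. At a baseline of 10^5/ml the E. coli window is one value wide, and a laboratory cap on counts could close most of it.

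A reader might infer several stronger things that the document does not support:

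- *That persistent infection is scored as cure.* The protocol's own idea of true infection is symptoms plus bacteriuria, and symptoms are judged in co-primary endpoint 1. What is shown is persistent significant bacteriuria.
- *That the endpoint is biased towards success, or loses sensitivity because a short course suppresses without clearing.* The errors run both ways, and nothing in the article says how a short course acts on counts at the control sample.
- *That a power loss can be computed.* Suppose 10% to 50% of uncleared patients in both arms met the fold rule. Then 90% v 75% would become 91% v 77.5% (0.90 + 0.10 × 0.1; 0.75 + 0.25 × 0.1) up to 95% v 87.5%, and the 15-point difference would shrink to between 13.5 and 7.5 points. But the 10% to 50% range has no basis in the article, the 15-point difference was hypothesised for clinical efficacy, and the reverse error is ignored. It is an illustration, not an estimate.
- *That patients without bacteriuria on day 0 spoil the denominator.* The intention-to-treat set omits the bacteriuria criterion by stated choice, and the NTT set, for which 113 was calculated, already requires significant bacteriuria.

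**Conclusion.** The definition of bacteriological cure is wrong as written. It contradicts the protocol's limit for significant bacteriuria and does not match the stated purpose of the control urines. The contradiction follows from the text alone, and it persists inside the NTT set.

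Its reach is bounded. Only patients with baselines of at least 10^5/ml (E. coli) or 10^6/ml (other uropathogens) can be scored as cured while significantly bacteriuric. Those with lower baselines can be scored as not cured while below the limit. Beyond that, the size is unknown: the article gives neither baseline nor control counts, so the proportion affected, the net direction and the effect on power cannot be stated.

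The direction would matter. The section on scientific and societal perspective contemplates concluding that 3 days is non-inferior. If the net effect were to count uncleared patients as cured in both arms, the observed difference could shrink towards that conclusion. That is conditional, not shown.

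**What to change.** Reconcile the two sections before the data are decoded:

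1. Define bacteriological cure as the day-0 uropathogen below the limit in Microbiological diagnostics at the first control sample: below 10^3/ml for E. coli, below 10^4/ml for other uropathogens. Counts at or above the limit are not cures.
2. Allow bacteriological relapse only after a cure in that sense. Same-organism growth that never fell below the limit is then persistence, not relapse.
3. Report the proportion with a fall of at least 100-fold as a secondary or sensitivity measure.

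The analysis sets need no change.

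The cost is a reworded definition. The three urine samples are already planned with counts, and the analysis is to be done on coded data, so no new procedure is needed. The one downside is small: comparison with any earlier study that used a fold rule moves from the co-primary endpoint to the secondary measure. The reported cure rate could move either way.

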### Study population

#### Inclusion criteria

Women in the age of 18–70 years old, with clinical features of community acquired uncomplicated LUTI, with the ability to understand the study and give consent, can participate. Patients need to have a symptom cumulative score of ≥2 p (i.e. none, mild, moderate or severe, scoring 0–3, respectively) in accordance to the validated questionnaires for uncomplicated UTI [16]. The following symptoms are included:Dysuria (i.e. pain or burning sensation when urinating)Urgency (i.e. feeling an increased and more frequent need to urinate)Pollakisuria/frequency (i.e. urinating more frequently than usually)

An accepted definition of uncomplicated LUTI is symptoms in concordance with uncomplicated LUTI and significant bacteriuria of uropathogenic bacteria [1], but we choose not to include the latter criteria in our intention to treat (ITT) analysis. This is because we want the included patients in the ITT group to mimic the realistic settings as much as possible (i.e. in which patients with uncomplicated LUTI will receive antibiotic therapy without urine samples in most primary care settings).

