## Data processing and statistical analysis

The source data is the GP’s and patient’s questionnaires and the diagnostics answers from the microbiological lab at the DCM. All source data will all be stored by the investigator and sponsor, in originals and scanned copies, at the DCM. The collected source data are transferred, logged and processed in the computers of the DCM. Analysis will be made in ITT, PP, and NTT form, respectively. All data will be analyzed coded, and only de-coded after the analysis is done and the analytic results are written in the relevant sections in the future article. The statistical software packages SAS (SAS Institute, Cary, NC) will be used for all analyses. Categorical data will be analyzed using a Fisher’s Exact test.

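### The bacteriological cure definition lets women with no bacteriuria at day 0 count as cured in the ITT and PP analyses of co-primary endpoint 2, pulling the difference towards zero

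*Protocol article*

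**What the plan says.** All references are to the protocol article.

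- **Primary endpoint.** Co-primary endpoint 2 is the "proportion of patients bacteriologically cured at first control urine sample". No baseline condition is attached.
- **Outcome, Definitions.** There are two routes to cure, joined by *or*. The first is relative: "Bacteriologically cured is defined as significant reduction", specified as at least a hundredfold decrease, which needs a day-0 count. The second is absolute: "potentially full eradication of uropathogenic bacteria (i.e. sterile culture or asymptomatic contaminations of non-uropathogenic bacteria". It is described entirely by the state of the control sample.
- **Inclusion criteria.** Entry is on a symptom score. On significant bacteriuria the authors write: "we choose not to include the latter criteria in our intention to treat (ITT) analysis". Their reason is to resemble ordinary primary care.
- **Power, sample size and analysis, Definitions.** "The intention-to-treat (ITT) analysis will be consisting of all included patients". PP is "all the patients that follow-up with clinical and bacteriological data (i.e. excluding the dropouts". Only NTT adds significant bacteriuria, and it also requires a mecillinam-susceptible isolate.
- **Data processing and statistical analysis.** "Analysis will be made in ITT, PP, and NTT form, respectively". Endpoint 2 is not confined to NTT, and no set is named as primary for it.

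**The concern.** Taken together, these rules classify a woman who had no uropathogen before treatment, and has none at the control sample, as a bacteriological cure in two of the three planned analyses of a co-primary endpoint. She had nothing to eradicate, so her result says nothing about treatment duration. The reason given for symptom-only entry supports the clinical co-primary endpoint. It does not explain why eradication should be scored where no organism was found.

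The relapse definition in the same section shows the gap from another side. It separates relapse from reinfection by whether the day-28 organism is the same as before. For a woman who was culture-negative at day 0 there is no earlier organism to compare.

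What is at stake is the estimate. Cure rates rise in both arms and the difference moves towards zero. The Discussion (Scientific and societal perspective) foresees keeping the 3-day regimen if it proves non-inferior. For that conclusion, a bias towards no difference is anti-conservative.

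**Working it through.** **1. The plan's own figures.** Inputs from Power analyze: 90% v 75%, two-sided 5%, power 0.80. The mean rate is 0.825.

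- Uncorrected: n = [1.96·√(2·0.825·0.175) + 0.8416·√(0.9·0.1 + 0.75·0.25)]² / 0.15² = (1.0532 + 0.4433)² / 0.0225 ≈ 99.5, so 100.
- With continuity correction: (99.5/4)·[1 + √(1 + 4/(99.5·0.15))]² ≈ 112.5, so 113, as stated for NTT.
- 113/0.7 = 161.4 (stated 161) and 161/0.7 = 230.0 (stated 230).

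The figures reproduce. The trial is sized on NTT, the set this problem does not touch.

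**2. Dilution formula.** Let f be the share of women who are culture-negative throughout, all scored cured in both arms, and p the cure rate in the rest. The observed rate is (1 − f)p + f. The observed difference is (1 − f) times the difference in bacteriuric women.

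**3. Range for f (an assumption).**

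- About 10%: the Background gives a 90% positive predictive value for clinical diagnosis. It is quoted for a fuller symptom picture than the entry score demands, so it is only a guide.
- At most 30%: 113/161 = 0.70, so the plan expects 30% of PP to be outside NTT. The plan calls this fall-out, and the step must also cover resistant isolates. Giving all of it to culture-negative women leaves no room for those.

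**4. Results with 161 per arm.** The 90% v 75% is borrowed: the plan states it for clinical efficacy and expects a larger bacteriological difference. Power is by exact enumeration of the planned two-sided Fisher test. The restricted n is 161(1 − f), rounded.

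| f | Observed rates as defined | Difference | Power, all 161 | Bacteriuric women per arm | Power, restricted |
|---|---|---|---|---|---|
| 10% | 91.0% v 77.5% | 13.5 | 90.1% | 145 | 90.7% |
| 20% | 92.0% v 80.0% | 12.0 | 85.3% | 129 | 86.8% |
| 30% | 93.0% v 82.5% | 10.5 | 78.8% | 113 | 81.7% |

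The power gap is 0.6, 1.5 and 2.9 points. A larger true bacteriological difference would shrink by the same factor 1 − f.

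**5. What restriction does not remove.** Step 4 gives every bacteriuric woman the 90% v 75% effect, but the plan sizes the susceptible-only set on those rates. Suppose the 30% of PP outside NTT splits into culture-negative women and women with resistant isolates, and that duration makes no difference in the latter (an assumption). The difference in all PP is then 15 × 0.70 = 10.5 points. Restricting to bacteriuric women gives:

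- 20% culture-negative, 10% resistant: 15 × 0.70/0.80 = 13.1 points;
- 10% culture-negative, 20% resistant: 15 × 0.70/0.90 = 11.7 points.

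Restriction removes the dilution from culture-negative women and leaves any dilution from resistance. The powers in step 4 make no allowance for resistance in either column.

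**The case against.** **The wording presupposes an organism.** Eradication, decrease and relapse with the same organism all suggest that something was there first, and a condensed article may leave evaluability rules to the full protocol or SAP. This tempers the point without removing it. The article spells out eradication as a state of the control culture, states the analysis sets, and nowhere makes a culture-negative woman non-evaluable. The rules it does state give the result described.

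**An undiluted analysis is already planned.** This stands in large part. NTT requires bacteriuria and is the set on which the sample size rests. But it is not named primary for endpoint 2, and because it drops resistant isolates, no planned set covers all bacteriuric women.

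**The average over all symptomatic women is a pragmatic quantity.** That is fair for the clinical endpoint. For a bacteriological endpoint it mixes clearance with the absence of infection.

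**Stronger readings that a reader might infer.**

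- *That the bacteriological comparison is invalid.* Dilution is expected equally in both blinded arms, so the type I error of the superiority test holds and the test is, if anything, conservative.
- *That power is seriously damaged.* The loss is at most about 3 points over the range examined.
- *That the three sets would disagree purely because of this definition.* They also differ by dropout and by susceptibility.
- *That restriction recovers the full 15 points.* Step 5 of the working shows that it need not.
- *That results in women with sub-significant day-0 counts are unrelated to treatment.* The documents do not show this; a low-count uropathogen in a symptomatic woman can still be cleared by treatment.

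**Conclusion.** The point holds as a defect in the definition for ITT and PP, and should be fixed. Under the stated rules, women never shown to be bacteriuric count as bacteriological cures. Both cure rates are inflated and the difference is multiplied by 1 − f. On the borrowed 90% v 75%, the loss is 1.5 points at f = 10% and 4.5 points at f = 30%; the latter is an upper bound that leaves no room for resistant isolates.

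The size rests on two assumptions: the value of f, which the documents do not give directly, and the use of clinical rates for a bacteriological endpoint. The direction rests on neither, provided that culture-negative women remain culture-negative at control.

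The practical harm is an estimate biased towards no difference, which matters most if ITT or PP is used to support non-inferiority of 3 days. ITT offers no protection there, because it carries the same dilution. The existing NTT analysis and the small power cost keep this below a flaw that must be resolved before the trial can be relied on.

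**What to change.** In the outcome definitions, state that bacteriological cure is evaluated only in women with significant bacteriuria in the pre-treatment sample, using the thresholds already given under Microbiological diagnostics (10³/ml for *E. coli*, 10⁴/ml for other uropathogens). For co-primary endpoint 2, use that denominator in both ITT and PP, whatever the mecillinam susceptibility. Report control cultures of women without day-0 bacteriuria separately. Keep the full ITT set for the clinical co-primary endpoint, where the realistic-practice argument applies.

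The day-0 culture is planned for every patient and is taken before treatment, so restricting all randomised women by it preserves the randomised comparison. NTT stays as it is for the susceptible-only question.

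The cost is a sentence or two in the definitions and no new data. The downsides are a smaller bacteriological denominator and lower quoted cure rates. Any dilution from resistant isolates would remain in the restricted ITT and PP analyses, and the report should say so.
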